#### Planned primary analysis.

Between-group comparisons (neuropathic pain vs no neuropathic pain) will be conducted using appropriate non-parametric tests (Mann–Whitney U test) where data are not normally distributed, or independent-samples t-tests where normality is satisfied.

Data from individual nociceptive fibres will be analysed with explicit consideration of clustering within participants. Where appropriate, fibre-level measurements will be summarised at the participant level (for example, by averaging) to provide an independent observation per participant for primary analyses. In addition, mixed-effects models will be used, with participant included as a random effect, to account for within-participant variability. Multiplicity arising from multiple outcomes will be addressed using appropriate multiple-comparison adjustments (for example, Bonferroni or false discovery rate correction).

This dual approach allows us to perform conservative primary analyses at the participant level by averaging, while also utilising more sophisticated modelling through a mixed-effects model that retains the detail of the individual fibre data while correcting for the dependence between fibres from the same participant. The mixed-effects model will bridge the participant (unit of inference) and individual fibre (unit of observation) without the statistical error of treating fibres from the same person as independent data points.

Multivariable logistic regression models will be used to examine the association between neuropathic pain status and microneurography-derived measures of axonal excitability and properties, adjusting for prespecified covariates (age, sex, diabetes status, neuropathy severity, and medication use).

Multicollinearity among predictors will be evaluated using variance inflation factors; when two predictors are highly correlated, the variable with greater variance or stronger biological relevance will be retained in the final model.

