#### Sample size justification.

Sample size calculations are based on power to identify differences in QST cluster frequencies and to support clustering and multivariate analyses.

- Using pilot quantitative sensory testing data from DOLORisk, expected cluster frequencies for diabetic distal symmetrical polyneuropathy are 53.9% (sensory loss), 25.0% (mechanical hyperalgesia) and 15.8% (thermal hyperalgesia). For non-diabetic neuropathies the corresponding frequencies are 49.7%, 21.2% and 14.5%.

- For moderate effects (Cohen’s d ~ 0.5) in the quantitative sensory testing cluster analyses, a total of 130 diabetic and 148 non-diabetic participants provides approximately 80% power at α = 0.05.

- For k-means and hierarchical clustering applied after principal component analysis, a conservative estimate requiring 2^8 = 256 participants was used to ensure adequate representation across variable permutations.

- A multivariate regression model with age, sex, diabetes status, neuropathy severity, and medication use will require 8 degrees of freedom to represent all its variables (assuming a categorical variable coding for 4 categories of medication). Allowing for at least 15 event per variable (EPV) we will require a sample size of at least 120 participants for model development. As described above, variable selection and filtering based on multicollinearity will likely increase the EPV.

- Taking these calculations together (and accounting for anticipated success rates in microneurography recordings: minimum 60% for diabetic participants and 80% for non-diabetic participants), the recruitment target is 272 participants (124 diabetic and 148 non-diabetic).

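### The regression sample size counts participants where its own rule counts events: 120 participants give at most 7.5 events per variable, not 15, and the listed variables include no microneurography measure

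*Protocol article*

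**What the plan says.** Under the sample size justification, the protocol article describes "A multivariate regression model with age, sex, diabetes status, neuropathy severity, and medication use" and says that it "will require 8 degrees of freedom to represent all its variables", taking medication as one categorical variable with four categories. It continues: "Allowing for at least 15 event per variable (EPV) we will require a sample size of at least 120 participants for model development". It then adds that "variable selection and filtering based on multicollinearity will likely increase the EPV".

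The planned primary analysis gives the model with that covariate list: "Multivariable logistic regression models will be used to examine the association between neuropathic pain status and microneurography-derived measures of axonal excitability and properties", adjusted for the same five covariates. Where two predictors are highly correlated, "the variable with greater variance or stronger biological relevance will be retained in the final model".

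The justification ends with a recruitment target of 272 (124 diabetic and 148 non-diabetic), allowing for minimum recording success rates of 60% and 80%. It gives no expected proportion with neuropathic pain for the recruited sample.

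**The concern.** An events-per-variable rule for a logistic model refers to the smaller of the two outcome classes. The plan multiplies parameters by events per variable and labels the product participants. For 120 participants to supply 120 events, every one of them would need to be in the same pain class, and there would be nothing to compare.

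The parameter count also looks short. The variables listed are the adjustment covariates only, while the model exists to relate pain status to microneurography measures.

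At stake is the reliability of an adjusted model that forms part of the planned primary analysis. A reader would take it to be supported by 15 events per parameter when the sample supports fewer. The remedy offered in the text, dropping collinear predictors, could remove a prespecified confounder or the measure under study.

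**Working it through.** **Inputs.** From the sample size justification: 8 degrees of freedom (df); 15 events per variable (EPV); 120 participants; target 124 + 148 = 272; minimum success rates 0.60 and 0.80. From the planned primary analysis: logistic model, pain status binary. The share p in the smaller pain class is not stated for this sample. Its mathematical maximum is 0.5. The introduction says about half of those with diabetic polyneuropathy have chronic neuropathic pain. A value of 0.3 is used below only as an assumed lower scenario.

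**Step 1: the plan's figure.** 8 × 15 = 120. It reproduces exactly, as a count of events.

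**Step 2: EPV with 120 participants.** EPV = N × p / df.

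| p | Events | EPV, 8 df | EPV, 9 df (one microneurography parameter added) |
|---|---|---|---|
| 0.5 (maximum) | 60 | 7.5 | 6.67 |
| 0.3 (assumed) | 36 | 4.5 | 4.0 |

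The bound of 7.5 needs no assumption about pain prevalence. It also holds if the 8 df already contain a microneurography term.

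**Step 3: evaluable participants needed for 15 EPV.** N = 15 × df / p.

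- 8 df: 120 / 0.5 = 240; 120 / 0.3 = 400.
- 9 df: 135 / 0.5 = 270; 135 / 0.3 = 450.

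**Step 4: what the target delivers.** Evaluable = 0.60 × 124 + 0.80 × 148 = 74.4 + 118.4 = 192.8.

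| p | Events | EPV, 8 df | EPV, 9 df |
|---|---|---|---|
| 0.5 | 96.4 | 12.05 | 10.71 |
| 0.3 (assumed) | 57.8 | 7.23 | 6.43 |

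The success rates are stated as minimums, so 192.8 is a floor. If all 272 gave usable recordings and the split were even, there would be 136 events: EPV 17.0 on 8 df and 15.1 on 9 df. With one measure in the model, 15 EPV needs 270 of the 272 recordings to succeed and a 50:50 split.

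**Step 5: the collinearity filter.** 15 EPV on 60 events allows 60 / 15 = 4 parameters. With medication as one four-category variable, the prespecified covariates need at least 7: age 1, sex 1, diabetes 1, severity at least 1, medication 3. Filtering could reach 15 EPV at N = 120 only by discarding prespecified covariates.

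The larger-variance criterion also depends on units. The same conduction velocity has 1000² = 10⁶ times the variance in mm/s that it has in m/s.

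**The case against.** The strongest reply is that 120 does not size the study. It is one line beneath larger requirements, and the target is 272. That stands, and it limits the severity. A reader might infer that the study as sized is overfitted, but the documents do not establish this: at the minimum success rates and an even split, one measure per model has about 10.7 EPV. The primary comparisons of participant-level summaries by t-test or Mann–Whitney test do not depend on this figure at all.

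Other stronger readings also go too far:

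- **A joint model of all the measures.** Adding the six measures named under the primary outcome comparisons to the 8 df gives 14 df, 14 × 15 = 210 events and 420 participants at an even split. But the plan speaks of models in the plural and offers its list of measures as examples. Nothing says that all six enter together.
- **Filtering can never raise EPV.** Selection driven by the outcome does not reduce the number of candidate parameters. A collinearity filter looks only at the predictors and can reduce it. The weakness of the plan's statement is that the gain is unquantified and cannot be large enough without losing prespecified covariates.
- **The adjustment set is decided by measurement scale.** The rule also offers biological relevance as a criterion. The unit dependence affects one branch of it and is a secondary point.
- **This is the only adjusted test of the primary hypothesis.** The article does not say whether the mixed-effects models carry covariates, so this cannot be asserted.

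Two further replies concern the reading of the text. First, the 8 df are not itemised. If severity takes one parameter, the covariates use 7 and one is left over. The text nevertheless assigns all 8 to a list containing only covariates, and the bound in step 2 holds either way. Second, 15 subjects per variable for a continuous outcome would make 120 participants coherent. But the text says events, the covariate list matches the logistic model, and the reference back to multicollinearity filtering points to the same section.

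**Conclusion.** The point holds as an error in a stated figure. The 120 is the number of events required on 8 df, not the number of participants. With 120 participants EPV is at most 7.5, half the stated 15, whatever the pain prevalence.

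The target of 272 narrows the gap but does not clearly close it: at the minimum success rates EPV is at most 12.05 (8 df) or 10.7 (9 df). The figures of 7.2 and 6.4 apply only if the smaller class is 30%, which is an assumption. Recording success above the stated minimums would raise all of these.

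The absence of a microneurography parameter follows from the variables listed, with the reservation that the df are not itemised. This should be fixed, but it does not invalidate the study's size.

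**What to change.** In the sample size justification:

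- Relabel 120 as events in the smaller pain class.
- Itemise the degrees of freedom, including one microneurography parameter per model.
- State the assumed proportion with neuropathic pain.
- Replace the claim of 15 EPV with the EPV that the planned evaluable sample delivers: about 10.7 at best with one measure per model on 9 df, at the minimum success rates. Keeping 15 EPV as a requirement would mean 135 events and at least 270 evaluable participants, which the plan does not expect at those rates.
- Remove the reliance on filtering to raise EPV.

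In the planned primary analysis:

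- Keep the prespecified covariates in the model whatever their variance inflation factors, and use those factors to report imprecision.
- Remove the larger-variance criterion.

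The cost is wording only. No extra participants are needed, and the stated EPV becomes less favourable.

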#### Statistical plan.

Analyses will address the relationships between neuropathy, neuropathic pain, quantitative sensory phenotype and microneurography measures of nociceptor excitability and axonal properties. Analyses will be prespecified, scripted for reproducibility and conducted using appropriate statistical software.

Continuous variables will be summarised using mean (standard deviation) or median (interquartile range) depending on distribution; categorical variables will be summarised using counts and percentages. Point estimators will be reported alongside their respective 95% confidence interval. All hypothesis tests will be two-tailed. Where multiple comparisons are performed, p-values will be adjusted using methods appropriate to the comparison (for example Bonferroni or false discovery rate), and this will be reported alongside unadjusted p-values.

The primary hypothesis is that participants with neuropathic pain will exhibit altered axonal properties and excitability compared to those without neuropathic pain. The primary outcome will therefore be a comparison of microneurography measures of axonal excitability and axonal properties between participants with and without neuropathic pain.

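### The recruitment target of 272 contradicts the plan's own requirements (130 diabetic; 256 for clustering) and shows no allowance for failed recordings

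*Protocol article*

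**What the plan says.** All the figures stand in the protocol article under Sample size justification.

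- Sensory-testing cluster analyses, at a standardised difference of about 0.5: "a total of 130 diabetic and 148 non-diabetic participants provides approximately 80% power".
- Clustering after principal component analysis: "a conservative estimate requiring 2^8 = 256 participants was used".
- Multivariable regression: 8 degrees of freedom at 15 events per variable, given as at least 120 participants.
- The closing step says it takes these calculations together, "accounting for anticipated success rates in microneurography recordings: minimum 60% for diabetic participants and 80% for non-diabetic participants", and concludes that "the recruitment target is 272 participants (124 diabetic and 148 non-diabetic".

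The Secondary analyses section shows which of these depend on a recording. Microneurography is one of the domains entering the principal component analysis that feeds the clustering. The comparison across sensory-testing groups has microneurography variables as its outcomes.

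**The concern.** The closing step claims two operations: combining the requirements and allowing for recordings that fail. Neither shows in the result. Combining them should give at least the largest requirement in each stratum, which is 130 diabetic and 148 non-diabetic. Dividing by a success rate below one should then raise both numbers. Instead one number is unchanged and the other is smaller.

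This is the only sample-size justification in the document, so a reader will take 272 as already protected against recording failure. If it is not, the clustering will run on clearly fewer participants than the plan says it requires. The comparison of microneurography variables across sensory groups may also fall short, depending on what 130 and 148 were meant to count.

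**Working it through.** **Inputs** (all from Sample size justification): requirements of 130 + 148, 256 and 120; success rates of 0.60 (diabetic) and 0.80 (non-diabetic); target of 124 + 148. I read the word for minimum as applying to both rates.

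**The plan's own sums.** 124 + 148 = 272, 2^8 = 256 and 8 × 15 = 120 are each correct. 130 + 148 = 278, which is not the target.

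**Can the target be reached from the requirements?**

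| Route | Diabetic | Non-diabetic | Total |
|---|---|---|---|
| No allowance | 130 | 148 | 278 |
| Requirement ÷ success rate | 130/0.60 = 217 | 148/0.80 = 185 | 402 |
| Requirement × (1 + failure rate) | 130 × 1.4 = 182 | 148 × 1.2 = 178 | 360 |
| Stated target | 124 | 148 | 272 |

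No route gives 124 + 148. The diabetic figure is 130 − 124 = 6 below its requirement (4.6%).

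**Participants with a usable recording at the minimum rates.**

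- Diabetic: 124 × 0.60 = 74.4
- Non-diabetic: 148 × 0.80 = 118.4
- Total: 192.8, about 193, which is 192.8/272 = 71% of recruits

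**Against each stated requirement.**

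- *Clustering, 256.* 192.8/256 = 75%, a gap of about 63. Reaching 256 from 272 recruits needs 256/272 = 94% overall success. At the planned mix, 256 with recordings needs 256/0.709 = 361.2, so 362 recruits. The range is 320 (all at 80%) to 427 (all at 60%).
- *Sensory-testing clusters, 130 + 148.* If only sensory-testing data are needed, the shortfall is the 6 diabetic participants. If the figures are meant for microneurography variables compared across sensory groups, about 74 and 118 are available.
- *Regression, 120.* 193 exceeds 120 if it counts participants. If it counts events, the answer depends on the split by pain status, which is not given. For example, if events are counted in the smaller pain group, that group is at most 96 of 193, or 96/8 = 12 per degree of freedom.

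**What the gaps mean for power.** As an illustration only, take two equal groups, a difference of 0.5 and two-sided 5%. Power is Φ(0.25·√N − 1.96):

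| N | Power |
|---|---|
| 130 | 81.3% |
| 124 | 79.5% |
| 118.4 | 77.6% |
| 74.4 | 57.8% |

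The 6-person gap costs under 2 percentage points. Recording failure in the diabetic stratum costs far more, where a recording is needed. The article does not name the test behind 130 and 148, so the equal split is my assumption.

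**The case against.** Several points on the other side have force.

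- **130 and 148 may not need recordings.** The plan ties them to sensory-testing clusters, and that testing is psychophysical. This stands. A reader might infer that 85 participants are missing against 278, or that 402 must be recruited. The documents support this only if 130 and 148 have to be participants with recordings, which they do not say.
- **130 and 148 may already be inflated.** 78/0.60 = 130 and 118/0.80 = 147.5, which rounds up to 148, so this cannot be excluded and it would make 402 a double inflation. Against it, the plan says these numbers themselves provide the power. An uninflated calculation also gives 148: mechanical hyperalgesia against the rest, one-sided 5%, (1.645 + 0.842)²/(0.25 × 0.212 × 0.788) = 148.0. That match is itself an inference and sits badly with "All hypothesis tests will be two-tailed". Neither route explains 124. What can be said is that the allowance is not visible, not that it was certainly never applied.
- **The rates are minimums.** This stands. About 193 is a floor, not a forecast.
- **The 6-person gap is trivial for power and could be a slip.** True, but the two numbers still conflict, and the slip would not explain the missing allowance.
- **Not every analysis is affected.** A reader might infer that no stated size is delivered. That is too strong: the regression figure is met if read as participants, and no size is stated for the primary comparison by pain status.
- **A cap on clustering dimensions.** A reader might conclude from 2^8 that 193 participants allow only seven components. The plan does not say that the 8 counts components, and it retains components by explained variance.

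**Conclusion.** Wrong as written. The section contradicts itself in two ways: the diabetic target is 6 below its own stated requirement, and an allowance for recording failure is claimed but cannot be seen in a target that fell. No other part of the article resolves this.

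The shortfall that matters is in the clustering: about 193 participants with recordings at the minimum rates against 256. It would disappear only at 94% overall success, where the stated minimums imply 71%. This rests on two assumptions: that the 256 must have microneurography data, as the clustering inputs imply, and that success is at the stated minimums. Whether the sensory-group comparison is also short depends on what 130 and 148 count.

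**What to change.** In Sample size justification, keeping 272 if that is what is feasible:

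1. Reconcile 130 with 124.
2. State whether 130/148 and 256 are recruited or evaluable numbers, and whether 130/148 concerns sensory-testing data alone or microneurography variables across sensory groups.
3. Give the evaluable numbers at the minimum success rates: about 74 diabetic and 118 non-diabetic, 193 in total (74.4 + 118.4 = 192.8).
4. Remove the statement that success rates are accounted for, or show the calculation.
5. Restate the clustering justification for about 193 participants instead of claiming 256.

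The cost is a rewritten paragraph and no extra participants. The downside is that the stated figures become less favourable.

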#### Risk of bias and mitigation.

Potential sources of bias include misclassification of fibre type, sampling bias, outcome reporting bias and confounding.

Fibre classification bias will be minimised using pre-specified, reproducible criteria based on activity-dependent slowing of conduction velocity. Sampling bias will be reduced by recording from multiple receptive fields per participant and using mixed-effects models to account for within-participant variability. Confounders will be adjusted for in regression models. The protocol and statistical analysis plan will be pre-specified and published to minimise outcome reporting bias.

### Data management

All study data will be recorded on case report forms and managed using REDCap. Identifiable data will be stored separately and securely, accessible only to authorised team members. Electronic data will be stored on secure, password-protected servers behind institutional firewalls; paper records will be kept in locked cabinets in secure areas. Data entries will be randomly checked for accuracy by an independent researcher (up to 30%).

As this is an observational study there is no external monitoring committee but we will internally monitor and regularly audit data collection and delivery of interventions. All research data and records will be stored in accordance with data protection and University of Oxford policies.
